### AIM 3. Evaluate the efficacy of the ISS-SBDOH intervention for improving virologic outcome and reducing high risk sexual activity and STIs

We hypothesize that the participants in the ISS-SBDOH arm will have a low level of viral load and reduced high-risk self-reported sexual activity and frequency of detectable STIs compared to the UC arm. GLMM and GAMM will be used to model viral load of patients and frequency of detectable STIs in the ISS-SBDOH arm and the UC arm across the contact periods (baseline and follow-ups) to evaluate an $$\:arm\times\:time$$ interaction. We also hypothesize that the differences in viral load, and level of high-risk sexual activity and frequency of detectable STIs between the ISS-SBDOH and the UC arms will be sustained during the 12-week post-integrated intervention follow-up period. GLMM/GEE and GAMM will be used to model the viral load, level of high-risk sexual activity, and frequency of detectable STIs between the two arms including parameterization that can distinguish the 16-week intervention phase and 12-week sustainability phase.

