### Secondary outcomes

(xxii)Plasma HIV viral load will be measured at baseline, and at weeks 4, 8. 12, 16, 20, 28 thereafter.(xxiii)High risk sexual activity will be assessed by survey of number of sexual partners, condomless sex, and screening of all orifices for chlamydia, gonorrhea and blood for syphilis.

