### Sample size calculation

Sample size calculation and power analysis were conducted based on the primary and secondary end points. For Aim 1, 55 subjects to be recruited in the ISS-SBDOH arm and 55 in the UC arm enable us to obtain stable point estimates and test the hypotheses for acceptability of the intervention program using one sample binomial approach. For the frequency and timeliness of SBDOH intervention and level of challenges, group sample sizes of 55 in the ISS-SBDOH arm and 55 in the UC arm will enable us to detect a difference as small as 0.5 in a continuous outcome (a medium Cohen’s effect size) with 80% power, and a significance level of 0.05 using a two-sided two-sample t-test. For Aim 2, using repeated measures analysis with intra-subject correlation of 0.1, a type I error of 0.05, a type II error of 0.2 (or 80% power), and average number of available data points 3.5, out of 5 data points (baseline, weeks 4, 8, 12, 16), 55 subjects in each of the two arms will enable us to detect a difference as small as 0.29 in standardized unit of the outcomes (e.g., adherence to ART) between the two arms, which is statistically and clinically meaningful. For Aim 3, for the binary outcome variable of viral suppression, using repeated measures analysis with similar set-up as Aim 2, the sample size of 55 participants in each of the 2 arms will be able to detect a 9% difference (or an odds ratio of 2.7) between the 2 arms (assuming 85% viral suppression at week 16 for control arm) and this effect size is considered clinically meaningful. Thus, the planned sample size should be sufficient for the proposed analyses.

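### Aim 3's sample-size figure is for a between-arm difference in viral suppression, but the test named for the virologic outcome is an arm-by-time interaction, which has far less than 80% power

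*Protocol article*

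**What the plan says.** The Sample size calculation section gives the Aim 3 justification "for the binary outcome variable of viral suppression, using repeated measures analysis with similar set-up as Aim 2". It says that 55 per arm "will be able to detect a 9% difference (or an odds ratio of 2.7) between the 2 arms". The usual-care rate behind that figure comes from "assuming 85% viral suppression at week 16 for control arm". The Aim 2 set-up carried over is "intra-subject correlation of 0.1, a type I error of 0.05, a type II error of 0.2 (or 80% power"), with "average number of available data points 3.5, out of 5 data points (baseline, weeks 4, 8, 12, 16"). No separate power figure is printed for Aim 3. The section closes by calling the planned size sufficient for the analyses proposed.

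The AIM 3 section says "GLMM and GAMM will be used to model viral load of patients and frequency of detectable STIs" in the two arms "across the contact periods (baseline and follow-ups) to evaluate an" arm-by-time interaction. It adds mixed, GEE and additive models that separate the 16-week intervention phase from the 12-week sustainability phase. Under Secondary outcomes, "Plasma HIV viral load will be measured at baseline" and at follow-up visits to week 28; suppression is not listed there as an endpoint.

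Aim 2, whose set-up is borrowed, is tested differently: the AIM 2 section puts an arm indicator in the model to test a difference in level.

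**The concern.** The power statement and the named analysis address different contrasts. A difference in level averaged over repeated visits gains precision from every visit. An arm-by-time interaction asks whether the arms diverge, so it has to estimate a change within each arm and pays for the noise in the baseline measurement. At a low within-person correlation such as 0.1, that cost is large.

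At stake is the closing statement that the sample size is adequate. If the interaction is the test reported, a null result could be read as evidence of no virologic benefit from a trial said to be adequately powered for a 9-point gain, when its chance of detecting that gain by this test was much lower.

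**Working it through.** **Inputs from the Sample size calculation section.** 55 per arm; control suppression 85%; difference 9 points, so 94%; correlation ρ = 0.1; 3.5 of 5 data points on average; alpha 0.05; 80% power. Two-sided testing is stated for Aim 1 only; I use two-sided 0.05 unless noted.

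**Assumptions (not in the document).** Exchangeable correlation; both arms at 85% at baseline; control flat at 85%; ρ varied from 0.1 to 0.7; two effect patterns and two codings of time, given below.

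**Step 1: reproduce the plan's figure.** The odds ratio for 94% against 85% is (0.94/0.06)/(0.85/0.15) = 2.76. Conversely, 2.7 implies 15.3/16.3 = 93.9%. The two stated effects agree.

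For a difference averaged over m points, the effective size per arm is 55m/(1 + (m − 1)ρ) = 55 × 3.5/1.25 = 154.

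SE = √[(0.85 × 0.15 + 0.94 × 0.06)/154] = √(0.1839/154) = 0.0346, and 0.09/0.0346 = 2.60.

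- Two-sided: Φ(2.60 − 1.96) = 74%. With a pooled null variance it is 73.3%, and 71.8% at an odds ratio of exactly 2.7.
- One-sided: Φ(2.60 − 1.645) = 83%. With a pooled null variance it is 82.7%, and 81.5% at 2.7.

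The Aim 2 figure behaves the same way: 0.29 SD has 81.6% power one-sided and 72.1% two-sided. A single-visit comparison of 55 against 55 would have only 34% two-sided. The stated figure is therefore an averaged between-arm difference, and it reaches 80% only one-sided. It also lets all 3.5 points carry the effect, although baseline is one of the five.

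**Step 2: the interaction, complete visits.** Time codings: (a) mean of the four post-baseline visits minus baseline; (b) linear slope with weights −2, −1, 0, 1, 2. Effect patterns: step (94% from week 4 on) and ramp (linear rise to 94% at week 16). For weights c, the variance per arm is Σᵢⱼ cᵢcⱼRᵢⱼsᵢsⱼ/55, with s² = p(1 − p) and R the correlation matrix.

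Worked case, coding (a), step, ρ = 0.1:
- Control: 0.1275 × [(1 + 3 × 0.1)/4 + 1 − 0.2]/55 = 0.1275 × 1.125/55 = 0.002608.
- Intervention: [0.0564 × 0.325 + 0.1275 − 0.2 × √(0.1275 × 0.0564)]/55 = 0.002343.
- SE = √0.004951 = 0.0704; power = Φ(0.09/0.0704 − 1.96) = 25%.
- Size for 80%: 55 × (2.8016 × 0.0704/0.09)² ≈ 264 per arm.

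Other cases at ρ = 0.1:
- (b), step: effect (−1 + 0 + 1 + 2) × 0.09 = 0.18, SE 0.187, power 16%.
- (b), ramp: effect 0.225, SE 0.190, power 22%.
- (a), ramp: effect 0.05625, SE 0.071, power 12%.
- Averaged difference over weeks 4-16, step: SE = √(0.1839 × 0.325/55) = 0.0330, power Φ(2.73 − 1.96) = 78%.

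Power by correlation (two-sided, complete visits):

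| ρ | Step: (a) | Step: (b) | Step: averaged | Ramp: (a) | Ramp: (b) | Ramp: averaged |
|---|---|---|---|---|---|---|
| 0.1 | 25% | 16% | 78% | 12% | 22% | 36% |
| 0.3 | 30% | 19% | 62% | 14% | 27% | 26% |
| 0.5 | 39% | 25% | 50% | 18% | 35% | 21% |
| 0.7 | 56% | 37% | 42% | 27% | 50% | 18% |

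With incomplete visits at ρ = 0.1, coding (a) under the step falls to 23% (2.5 post-baseline visits; about 288 per arm for 80%) and the slope under the ramp to 17% (3.5 of 5 visits).

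**Step 3: viral load as a continuous outcome.** The document gives no SD or target difference. Borrowing Aim 2's 0.29 SD as an assumption, coding (a) under the step has 27-30% power at ρ = 0.1 and 65-70% at ρ = 0.7, still below 80%.

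**The case against.** Four points on the other side have weight.

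1. Suppression is a dichotomy of the viral load that is measured, a generalised mixed model accepts a binary response, and the Randomization section already uses a detectable/undetectable split. A reader might infer that suppression will not be analysed, or that viral load will be modelled as a continuous variable crowded at the assay limit. The article does not say either, and the cut-off, transformation and handling of values below the limit belong to an analysis plan that is not shown. This answers most of the outcome mismatch but leaves the contrast mismatch.
2. The AIM 3 hypothesis is worded as a level compared with usual care, and the phase-specific models could carry an arm difference. So a reader should not infer that the interaction is the only Aim 3 analysis, or that a true 9-point gain will be missed whatever is done. But the interaction is the only test the section names, and nothing says an averaged difference will be tested or will take precedence.
3. The size of the shortfall depends on the coding of time and the shape of the effect, neither of which the article gives. Nor is the averaged contrast always better: under a ramp the linear interaction equals or beats it from a correlation of 0.3, and at 0.7 coding (a) beats it even under a step. This stands and limits the argument for averaging. It does not rescue the power statement, because no interaction scenario tried reaches 80%.
4. The 80% is not printed for Aim 3. It comes through the reference to Aim 2's set-up, and is best described as inherited.

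**Conclusion.** The point holds as a mismatch of contrasts. The Aim 3 figure describes a between-arm difference in suppression averaged over visits, the analysis named is an arm-by-time interaction on viral load, and the claim of sufficiency is not supported for that test. At the document's own correlation the interaction has about 12-25% power for the stated effect, depending on pattern and coding. The highest value found for suppression is about 56%, at an assumed correlation of 0.7.

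Even the powered contrast falls short of 80% two-sided: about 78% with complete visits and a step effect, and 72-74% with the stated 3.5 points.

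These figures assume exchangeable correlation, equal baselines and a flat control arm. The direction of the finding does not depend on which effect pattern or coding is chosen; the exact shortfall does. Aim 3 is secondary, so the primary outcomes are not affected.

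**What to change.** In the AIM 3 section, name viral suppression as the virologic outcome. Test the between-arm difference over the intervention visits, adjusted for the baseline detectable/undetectable stratum, and make the arm-by-time interaction supportive.

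In the Sample size calculation section, state the two-sided power for that contrast, with the number of post-baseline visits and the correlation assumed. The figures above are unadjusted, so the power should be computed for the adjusted model.

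If the team expects the effect to build slowly and prefers the interaction as the lead test, it can keep it, but should then replace the Aim 3 figure with the power for the interaction, giving the time coding and expected pattern.

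Either way the cost is wording, plus a less favourable stated power. No extra data or participants are needed.

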### Sample size calculation

Sample size calculation and power analysis were conducted based on the primary and secondary end points. For Aim 1, 55 subjects to be recruited in the ISS-SBDOH arm and 55 in the UC arm enable us to obtain stable point estimates and test the hypotheses for acceptability of the intervention program using one sample binomial approach. For the frequency and timeliness of SBDOH intervention and level of challenges, group sample sizes of 55 in the ISS-SBDOH arm and 55 in the UC arm will enable us to detect a difference as small as 0.5 in a continuous outcome (a medium Cohen’s effect size) with 80% power, and a significance level of 0.05 using a two-sided two-sample t-test. For Aim 2, using repeated measures analysis with intra-subject correlation of 0.1, a type I error of 0.05, a type II error of 0.2 (or 80% power), and average number of available data points 3.5, out of 5 data points (baseline, weeks 4, 8, 12, 16), 55 subjects in each of the two arms will enable us to detect a difference as small as 0.29 in standardized unit of the outcomes (e.g., adherence to ART) between the two arms, which is statistically and clinically meaningful. For Aim 3, for the binary outcome variable of viral suppression, using repeated measures analysis with similar set-up as Aim 2, the sample size of 55 participants in each of the 2 arms will be able to detect a 9% difference (or an odds ratio of 2.7) between the 2 arms (assuming 85% viral suppression at week 16 for control arm) and this effect size is considered clinically meaningful. Thus, the planned sample size should be sufficient for the proposed analyses.

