**Fig. 1 Fig1:**
[figure not shown]
SPIRIT figure for the trial Medical. STI and Treatment History

The overall flow of the study is shown in Fig. 2. This study is an open-label unblinded randomised control trial. Participants will be randomly assigned by 1:1 allocation to either: (1) the ISS-SBDOH arm, which will include training on how to use the ingestible sensor system (the ID-Cap from etectRx), data collection procedures, and schedules; or (2) the Usual Care (UC) arm, which will not use of ID-Cap system. On-boarding procedures will be done for both study arms. In the first 20 weeks, we will collect data on primary end points of acceptability of the ISS-SBDOH intervention, frequency and timeliness of SBDOH intervention, level of challenges of SBDOH in HIV treatment, and adherence to ART; the secondary end points will include viral load, high risk sexual activity and frequency of detectable sexually transmitted infections (STIs); and other measures. Durability of any observed effects from the ISS-SBDOH intervention will be evaluated during a 12-week post-ID-Cap system follow-up period. The trial will be conducted in accordance with the guidelines for Good Clinical Practice (GCP) and will satisfy Consolidated Standards of Reporting Trials (CONSORT) reporting conventions [27].

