### SBDOH Intervention

Like many urban safety net HIV clinics, enrollment clinical site personnel (nurses, case workers, and social workers) can provide services for SBDOH needs by a multidisciplinary team. Figure 3 summarizes how this service can be activated in the intervention arm. In UC arm, patient identification/referral is initiated during a clinic visit, or if a patient reaches out between visits to their primary provider or a member of the multidisciplinary team. Once triggered, the team will meet with the participant to assess SBDOH and use resources and expertise available to address key issues. The team members are experienced and when appropriate can provide referrals to dedicated HIV mental health specialists. The social workers and case managers are experienced at addressing social/behavioral determinants, including but not limited to in- or out-patient substance use disorder, housing, and food insecurity. The mental health specialists are also focused on and experienced in addressing the challenges PLWH encounter, including anxiety, primary psychiatric conditions, as well as stigma and discrimination. However, this signal to address SBDOH needs often occurs weeks to months after issues have emerged. In this study, the SBDOH intervention will be triggered if a participant has missed his/her prescribed ARVs for a total of 3 days within a five-day period monitored by real-time sensor. In addition, during the first 16 weeks, the participants in the intervention group will use ID-Cap to monitor their daily HIV adherence in real-time and receive their pre- and post- dosage reminders. With 4-week intervals, we will ask participants for their feedback on ID-Cap and/or the SBDOH session, when applicable.

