## Outcomes

### Primary outcome

(i)Acceptability of the integrated intervention will be measured at baseline, and around week 4, 8, 12, and 16, evaluated by quantitative measures interviews. The items in the quantitative measure will be rated on a five-point Likert scale ranging from very strongly disagree to very strongly agree. Acceptability will be measures in terms of: overall satisfaction (would recommend to friend, would use outside of study setting, satisfied with system), utility, and specific items such as helpfulness and convenience. In addition, we will ask participants to rate items specific to the ID-Cap system (comfort of wristband, comfort receiving text messages).(ii)Frequency and timeliness of SBDOH intervention, level of challenges of SBDOH in HIV treatment will be measured at baseline, and around week 4, 8, 12, 16, 20, and 28. We will collect SBDOH measures, such as economic stability (e.g., food security), health (e.g., gap in health coverage), neighborhood and built environment (e.g. transportation needs), social and community context (e.g., violence, and criminal justice involvement), and substance and alcohol use, sexual behavior, and other health related behaviors. Challenges of SBDOH will be measured as the count of SBDOH issues one is facing, and the degree of each issue (e.g., low/medium/high with housing challenge determined by nurse or care coordinator) with summary scores. Frequency and timeliness of SBDOH intervention are measured as number of sessions, and time to first, and subsequent sessions, if applicable, from baseline, and others. This information will also be collected when intervention is triggered by the monitoring system.(iii)Adherence to ART measured by ID-Cap system for 16 weeks.(iv)Self-Reported Medication Adherence [34]. We will use a widely used measure of percent of prescribed dose taken during the preceding seven days. We will also measure patterns of dosing (e.g., patterns of consecutive missed doses in the past two weeks).

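### The 80% power stated for timeliness comes from a t-test on 55 complete values per arm, but time to an SBDOH session is right-censored for anyone who has none

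*Protocol article*

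**What the plan says.** The Sample size calculation section treats three outcomes as one. It reads "For the frequency and timeliness of SBDOH intervention and level of challenges, group sample sizes of 55 in the ISS-SBDOH arm" and 55 in the usual care arm, and says that these numbers can "detect a difference as small as 0.5 in a continuous outcome" "with 80% power, and a significance level of 0.05 using a two-sided two-sample t-test".

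Other sections define what is being sized:

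- **Primary outcome, item (ii):** frequency and timeliness are "measured as number of sessions, and time to first, and subsequent sessions, if applicable, from baseline, and others". They are measured at baseline and around weeks 4, 8, 12, 16, 20 and 28.
- **SBDOH Intervention, intervention arm:** "the SBDOH intervention will be triggered if a participant has missed his/her prescribed ARVs for a total of 3 days within a five-day period".
- **SBDOH Intervention, usual care arm:** a session follows identification or referral at a clinic visit, or contact made by the patient between visits.
- **Table 1:** eligibility extends to people who are only at high risk of sub-optimal adherence or who have known SBDOH challenges.
- **Aim 1:** the between-arm hypothesis includes better timeliness in the intervention arm.
- **Statistical analyses:** the analysis is by intention to treat.
- **Discussion (limitations):** fully parametric analyses are mentioned, with time until the first session as the example.

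**The concern.** A two-sample t-test on 55 per arm assumes an observed value for every participant. Time to first session does not meet that assumption. A participant who never meets the missed-dose pattern, or a usual care participant who is never referred and never makes contact, reaches the end of follow-up with a time known only to exceed the window. The outcome definition itself concedes this with its "if applicable" qualifier ("time to first, and subsequent sessions, if applicable, from baseline").

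For such an outcome, power depends on the number of first sessions and the ratio of session rates. The article gives neither. At stake is a power figure, attached to part of a primary outcome and to a named between-arm hypothesis, that was derived for a different kind of variable. A reader cannot tell from it whether 110 participants are enough for the timeliness comparison.

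**Working it through.** **Inputs from the article:** 55 per arm with 1:1 allocation; standardised difference 0.5; two-sided α = 0.05; stated power 80%; two-sample t-test.

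**Step 1. The stated figure, taking complete data for granted.**

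Normal approximation: power = Φ(d·√(n/2) − 1.96) = Φ(0.5 × √27.5 − 1.96) = Φ(2.622 − 1.960) = Φ(0.662) = 74.6%. The exact noncentral t gives 73.8%.

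For 80% power at d = 0.5 the exact calculation needs 64 per arm. With 55 per arm the detectable difference at 80% power is 0.539 SD, which agrees with the stated 0.5 only after rounding to one decimal. This discrepancy is separate from censoring and applies to all three outcomes in the sentence.

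**Step 2. Does the t-test describe timeliness?**

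| What the t-test needs | What the article provides |
|---|---|
| An observed time for all 55 in each arm | A time only for those who have a session |
| Sessions certain to occur | Sessions conditional on a missed-dose pattern (intervention) or on referral or patient contact (usual care) |
| Everyone eligible bound to need a session | Entry also open to people only at risk of poor adherence |

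The calculation does not carry over. For those without a session the time is right-censored at the end of the window.

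**Step 3. What power depends on instead.**

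For a log-rank or Cox comparison with equal allocation, Schoenfeld's formula gives power = Φ((√D / 2)·ln HR − 1.96), where D is the number of participants with a first session. The detectable hazard ratio at 80% power is HR = exp(2 × (1.960 + 0.842) / √D) = exp(5.603 / √D). A hazard ratio above 1 means earlier sessions in the intervention arm.

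The article gives neither D nor HR, so both are assumptions shown over a range:

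| First sessions D (of 110) | 5.603/√D | HR detectable at 80% | Power if HR = 1.5 | Power if HR = 2 |
|---|---|---|---|---|
| 44 | 0.845 | 2.33 | 27% | 63% |
| 55 | 0.756 | 2.13 | 32% | 73% |
| 77 | 0.639 | 1.89 | 43% | 86% |
| 110 | 0.534 | 1.71 | 57% | 95% |

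Across these assumptions power runs from 27% to 95%. The 80% in the article corresponds to no identified row, and the range lies on both sides of it.

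**Step 4. The window.**

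D also depends on when observation stops. The Study duration section says the missed-dose trigger does not operate in the 12 weeks after the intervention, but that sessions can still arise through visits, provider contacts or participant calls. The outcome definition measures timeliness to week 28. Censoring at week 16 and at week 28 would therefore give different event counts and could give different hazard ratios. The sample size section does not say which applies.

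**The case against.** The strongest reply is that the sentence is a planning approximation for three outcomes together, and that the survival model and the handling of participants without a session belong in a statistical analysis plan. The Discussion does foresee a parametric analysis of time to first session. That is fair as far as the analysis details go, and their absence is not the point here. But the article does attach a test, a sample size and a power to timeliness by name. The Discussion passage gives no event count or hazard ratio, so it does not repair that figure.

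A second reply is that a t-test can be kept close to valid by retaining everyone and setting the missing times to the end of the window. In simulations with assumed exponential times, a 16-week window and a hazard ratio of 2, this gave 54% power against 61% for log-rank when 30% of usual care had a session, and 76% against 82% when 50% did. The loss is modest under those assumptions, and the order can reverse if the extra sessions come early. This stands: the choice of test is not by itself ruinous. It does not restore the stated 80%, because the standardised difference would then depend on the unstated share with a session.

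A reader might go further and infer that the t-test will be run only on those who had a session, so that a real effect would almost never be found. The article does not support that. No section plans such an analysis, it would sit badly with the intention-to-treat statement, and its power depends heavily on the assumed distribution of times and on the window.

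**Conclusion.** The point holds in a limited form. The 80% stated for timeliness is the claimed power of a t-test on complete continuous data, and timeliness as defined is a time-to-event outcome with censoring possible in both arms.

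The direction of the error is not known. The true power may be above or below 80%, so it cannot be said that the trial is underpowered for timeliness. What can be said is that the detectable hazard ratio at 80% power lies between about 1.71 (everyone has a session) and 2.33 (44 first sessions), and is larger with fewer. These figures assume proportional hazards, equal allocation and a two-sided 0.05 level with no multiplicity adjustment.

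The conclusion that the stated power does not belong to this outcome needs none of those assumptions. It follows from the article's own definition of timeliness and its conditions for a session.

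**What to change.** In the Sample size calculation section:

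1. Remove timeliness from the t-test sentence.
2. State that time to first session will be compared in all randomised participants by a log-rank test or Cox model, stratified by the two randomisation factors (single or multiple tablet regimen, and detectable or undetectable baseline viral load).
3. State the window at whose end participants without a session are censored, either the 16-week intervention phase or week 28. Reconcile it with the Study duration section and the measurement schedule under Primary outcome.
4. Give the expected share with a first session in each arm, and the hazard ratio detectable at 80% power over a range of counts: about 2.33 with 44, 2.13 with 55, 1.89 with 77 and 1.71 with 110.
5. While the sentence is open, correct it for the outcomes that stay in it: about 74% power at 0.5 SD, or 80% power at 0.54 SD.

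The cost is wording only. Session timing is already collected and the sample size need not change. The downside is that the stated power becomes less favourable if few participants have a session.

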**Methods:**

In this protocol paper, we describe the design and procedures for a National Institutes of Health-funded randomized controlled trial that tests an innovative, integrated intervention combining the latest pill ingestible sensor system (the ID-Cap from etectRx) and strategies to address SBDOH. The intervention will trigger real-time actions to rapidly address SBDOH-related barriers when pre-specified patterns of poor adherence are detected (antiretroviral doses missed on three days within a five-day period). A cohort of 110 PLWH who have, or are at high risk for, sub-optimal adherence will be recruited from an HIV clinic in Los Angeles County. Participants will be randomized into the ingestible sensor intervention arm or the usual care arm. The intervention will run for 16 weeks, followed by a 12-week post-intervention period to evaluate sustainability. The primary outcomes are acceptability of the integrated intervention, frequency and timeliness of SBDOH intervention, level of challenges of SBDOH in HIV treatment, adherence to ART measured by ID-Cap system, and self-reported medication adherence. Secondary outcomes are plasma HIV viral load and high risk sexual activity,

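### Aim 1 power statement: 55 per arm gives about 74% power at d = 0.5, not 80%; 80% power is reached at 0.54 SD

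*Protocol article*

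**What the plan says.** The Protocol article plans 1:1 allocation, and its abstract gives the total: "A cohort of 110 PLWH who have, or are at high risk for, sub-optimal adherence will be recruited". Under Sample size calculation, the part of Aim 1 that compares the arms on frequency and timeliness of SBDOH intervention and on level of challenges reads: "group sample sizes of 55 in the ISS-SBDOH arm and 55 in the UC arm will enable us to detect a difference". The stated capability is to "detect a difference as small as 0.5 in a continuous outcome", which the article labels a medium effect on Cohen's scale (so it is in SD units), and the operating characteristics are given as "with 80% power, and a significance level of 0.05 using a two-sided two-sample t-test".

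For this calculation the article names no repeated measures, no baseline adjustment and no allowance for missing data. The repeated-measures set-up appears only for Aims 2 and 3. The section closes by judging the planned sample size sufficient for the proposed analyses.

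**The concern.** Sample size per arm, effect size, alpha, sidedness and test together determine the power, so the stated 80% can be checked directly. A standardised difference of 0.5 at two-sided 0.05 and 80% power is a familiar benchmark that calls for slightly more than 60 per arm, so 55 looks too few.

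The Outcomes section lists these measures among the primary outcomes, the Aim 1 analysis section states between-arm hypotheses for them, and this sentence is the only power statement that covers them. If it is wrong, the chance of missing a true difference of 0.5 SD under the stated test is about 26% rather than 20%, and the closing statement of sufficiency rests, for these outcomes, on a figure that the named calculation does not give.

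**Working it through.** **Inputs, all from the Aim 1 text of Sample size calculation:** n = 55 per arm; d = 0.5; alpha = 0.05, two-sided; two-sample t-test; stated power 80%.

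**1. Power at the stated inputs.**
- Noncentrality: d × √(n/2) = 0.5 × √(55/2) = 0.5 × 5.244 = 2.622.
- Normal approximation: Φ(2.622 − 1.960) = Φ(0.662) = 0.746.
- Noncentral t with 2 × 55 − 2 = 108 degrees of freedom: 0.738 (0.7385 to four places).

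The stated 80% is not reproduced. The shortfall is 5 to 6 points, and the probability of a miss at d = 0.5 is 1 − 0.738 = 0.262.

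**2. Difference detectable with 80% power at 55 per arm.**
- Normal approximation: (1.960 + 0.842) × √(2/55) = 2.802 × 0.1907 = 0.534.
- Noncentral t: 0.539.

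**3. Sample size for 80% power at d = 0.5.**
- Normal approximation: 2 × 2.802² / 0.5² = 62.8, so 63 per arm.
- Noncentral t: 63.8, so 64 per arm (power 79.5% at 63 and 80.1% at 64). In total 2 × 64 = 128, against 110 planned.

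**4. Other readings that might give 80%.**

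| Reading | Result | Fits the text? |
|---|---|---|
| One-sided 0.05 | 83.2% power; 50 to 51 per arm for 80% | No: the test is stated as two-sided, and the result is not 80% |
| Two-sided 0.10 | 83.2% power | No: 0.05 is stated |
| 0.5 as a raw difference | Needs SD = 0.5/0.539 = 0.93 | No: the text calls it a Cohen's effect size and gives no SD |
| 0.54 rounded to 0.5 | Possible origin | Still inaccurate as a lower limit; Aim 2's effect is given to two decimals (0.29) |

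None of these makes the sentence correct as it stands.

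**The case against.** The strongest reply is that the t-test is only a simplification. For level of challenges, the Aim 1 analysis section plans a GLMM over repeated visits, which may be more precise than a single comparison of means. As an illustration, suppose 3.5 data points per person (borrowed from Aim 2), equal correlation ρ between visits, and a time-averaged arm difference. The detectable difference is then 0.539 × √((1 + 2.5ρ)/3.5): 0.43 SD at ρ = 0.5 and 0.50 SD at ρ = 0.8. Alternatively, adjustment for a baseline value correlated about 0.37 with the outcome would bring 0.539 down to 0.5, since 0.539 × √(1 − 0.37²) = 0.50.

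This part stands: the design may well reach 0.5 SD for level of challenges under the planned model, so the shortfall should not be carried over to that outcome as though a t-test were the final analysis. But these correlations are assumptions that the protocol does not make for Aim 1. The illustration concerns an average difference rather than a slope, and it does not help frequency or timeliness of sessions. Nor does it make the stated t-test figure right.

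A second reply is that the gap is small and 0.5 is only a conventional benchmark; the article calls the Aim 2 and Aim 3 effects clinically meaningful, but not this one. That is fair, and it bears on how serious the error is, not on whether there is one.

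A reader might go further the other way and infer that power is much lower still, because Aim 2 assumes an "average number of available data points 3.5, out of 5 data points (baseline, weeks 4, 8, 12, 16". Taking 3.5/5 = 70% of 55, about 38 per arm, would give 58% power at 0.5 and a detectable difference of about 0.65 SD. The document does not support that inference. The 3.5 is an average number of repeated data points per participant for Aim 2, not the share of participants who can be analysed for Aim 1. The Outcomes section defines frequency and timeliness as number of sessions and time to sessions, with information also collected when a session is triggered, so a missed survey visit does not simply remove a participant. Level of challenges is modelled over several visits. The 58% and 0.65 figures therefore describe an analysis that the protocol does not plan.

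**Conclusion.** Wrong as written; it should be fixed. Under the inputs in the sentence itself, power at d = 0.5 is about 74%, not 80%; 80% power corresponds to 0.54 SD; and 80% power at 0.5 would take 64 per arm. The error is about 6 points of power, or 0.04 SD.

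This rests on the stated t-test with all 55 per arm observed, an SD-scaled outcome, and alpha of 0.05 applied to one outcome without correction, as the sentence has it. It shows that the published figure is incorrect. It does not show that the trial is inadequately powered under the planned mixed model, or that recruitment must rise to 128.

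**What to change.** Restate the Aim 1 sentence along these lines: with all 55 participants per arm observed, a two-sided two-sample t-test at 0.05 has about 74% power for a standardised difference of 0.5, or 80% power for a difference of 0.54. If a repeated-measures calculation was intended for level of challenges, name that method and give its inputs (number of data points, within-person correlation, and the contrast tested), and keep the t-test figure for frequency and timeliness.

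The cost is one sentence and a slightly less favourable figure. Sample size, endpoints and analysis can stay as they are.
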